### Functional Near-Infrared Spectroscopy

fNIRS will be completed before treatment, within 1 week following the 4-week treatment, and then at 1 month and 3 months post treatment. The TechEn (TechEn, Inc) system and a headcap with transmit and receive fibers positioned over the parietal and frontal lobes will be used (Figure 2). Data will be collected for 5 minutes at rest and then during a finger tapping exercise and working memory tasks. The resting task will consist of the participant sitting and resting while fixating on a small white cross for 5 minutes [37,38]. Finger tapping will be used as a simple, repeatable motor activation task, which has prominently shown a motor response [18,19]. The finger tapping exercise will consist of the participant tapping their right forefinger to their thumb at a frequency of 1 Hz, while being prompted on screen by “Tap” or a white cross indicating rest. The participant will alternate between tapping for 10 seconds and resting for 15 seconds, which will be repeated 10 times. Finally, the working memory task will consist of a 2-back variation of the n-back exercise [39], where a series of letters will appear on screen in 2-second intervals, and the participant will be asked to match each new letter to the letter presented 2 trials back. If the letters match, the participant is asked to press the right arrow key indicating correct, or, if the letters do not match, they are asked to press the left arrow key indicating incorrect. The participant will alternate between 20 presentations of letters followed by 20 seconds of rest, which will be repeated 3 times. Data on caffeine and other substance consumption from the last 8 hours before fNIRS assessment will also be collected. This protocol was adapted from the protocol described by Hocke et al [18].

**Figure 2 figure2:**
[figure not shown]
Optode configuration of functional near-infrared spectroscopy headcap based on 10-10 and 10-5 electroencephalogram coordinate system. AF: anterior frontal; AFF: anterior prefrontal; C: central; CP: central parietal; F: frontal; FC: fronto-central.

### Rivermead Postconcussion Symptom Questionnaire

The RPQ is the primary outcome measure for this study. The RPQ assesses the severity of 16 commonly experienced PPCS symptoms. The participants are instructed to rate the extent to which they have suffered from each of the listed symptoms in the past 24 hours, as compared to preinjury levels, using a scale of 0 (“not experienced at all”) to 4 (“a severe problem”). It is advised to use this assessment as 2 separate scales (RPQ-13 and RPQ-3). Using these subscales, the instrument has good test-retest reliability and external construct validity [40]. This questionnaire probes the separate cognitive, emotional, and somatic components of PPCS.

### Exploratory Outcome Measures

Multiple other questionnaires will be administered as exploratory outcomes. The questionnaires administered will be described in the following section.

#### Quality of Life After Brain Injury Questionnaire

Quality of life will be measured by the quality of life after brain injury (QOLIBRI) questionnaire assessment. The QOLIBRI questionnaire is a health-related quality of life instrument developed specifically for participants who have experienced a traumatic brain injury. It has 6 subscales with a total of 37 items and is scored from 0 to 100 (with 100 being the best possible quality of life). This tool has been validated in the traumatic brain injury literature and is shown to have adequate (>0.5) to excellent (>0.7) test-retest reliability [41].

#### Headache Impact Test

The headache impact test-6 (HIT-6) is a 6-item tool used as a global measure of headache impact. The HIT-6 addresses the 6 categories of headache impact including social functioning, role functioning, cognitive functioning, vitality, psychological distress, and severity of headache pain. Each question is scored on a 5-point scale. The total score can range from 36 to 78, with higher total score indicating greater impact [42]. The HIT-6 has been validated in participants with episodic and chronic migraine [43]. Based on a chronic tension type headache study, a minimal clinically important change has been reported as a decrease of at least 8 points on the HIT-6 [44].

#### Patient Health Questionnaire-9

The patient health questionnaire-9 (PHQ-9) is a 9-item tool used to assess the presence and severity of depressive symptoms. In the PHQ-9, a score below 4 is classified as minimal, 5 to 9 is mild, 10 to 14 is moderate, 15 to 19 is moderate-to-severe, and anything higher than 20 is severe [45]. The PHQ-9 has been validated in participants with mild to severe traumatic brain injury with a screening cut-off score of greater than 12 for major depressive disorder [46]. The test-retest reliability is excellent within 7 days of the initial assessment. The minimal clinically important difference for the PHQ-9 is 5 points [47].

#### Generalized Anxiety Disorder Scale

The generalized anxiety disorder (GAD-7) scale is a 7-item tool where, like the PHQ-9, each item is rated on frequency over a 2-week period based on a 0 to 3 scale [48]. An analysis confirmed screens for depression (PHQ-9) and anxiety (GAD-7) to be distinct, and it is suggested that the 2 highly comorbid disorders be assessed independently [49].

#### Saint Louis University Mental Status Exam

The Saint Louis University mental status exam will be used to screen the participants for mild cognitive impairment. The Saint Louis University mental status exam is an 11-item scale with questions that correspond to attention, recall (immediate and delayed with interference), orientation, number calculation, memory, registration, visual spatial information, and executive function [50].

#### Screening for Somatoform Symptoms Conversion Disorder Subscale

Somatoform symptoms will be monitored through the screening for somatoform symptoms conversion disorder subscale. This screening lists 14 symptoms associated with somatization disorder. Each symptom is rated on degree of impairment experienced in the past 7 days on a 0 to 4 scale, with 0 indicating “not at all” and 4 indicating “very severe” [51].

#### Posttraumatic Stress Disorder Checklist for DSM-5

The posttraumatic stress disorder (PTSD) checklist for Diagnostic and Statistical Manual of Mental Disorders, Fifth Edition (DSM-5; PCL-5) is a screening tool used to assess PTSD. The PLC-5 is a 20-item self-report measure with each question scaled from 0 to 4, with the total score ranging from 0 to 80. A score greater than 53 may indicate more severe PTSD symptoms [52].

### Analysis

#### Preprocessing fNIRS Data

All preprocessing data will be done using MATLAB (The MathWorks Inc). Raw intensity data will first be converted to optical density using Homer3 (hmrR_Intensity2OD). Optical density will then be assessed for signal quality over several steps. First, channels that display low signal (below 90 dB) or have an oversaturated signal (above 140 dB) will be discarded. Channels that have a signal to noise ratio less than 1 will also be discarded, as previously described by Hocke et al [18]. Next, a spline motion correction step will be applied to correct for motion artifacts and baseline shifts using Homer3 (hmrR_MotionCorrectSpline). Short distance detectors located approximately 8 mm from select sources will be used to remove the influence of extracerebral signal obtained from superficial layers [53,54]. A bandpass filter will be applied to the data with a low pass filter of 0.01 Hz and a high pass filter of 2 Hz (hmrR_BandpassFilt). Optical density data will then be converted to delta concentration of oxyhemoglobin and deoxyhemoglobin using the modified Beer-Lambert law with age-dependent differential path length factors. Finally, the concentration data will be down sampled to 5 Hz.

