**Objective:**

The primary objective of this research is to determine whether rTMS treatment improves symptom burden in patients with PPCS compared to sham treatment using the Rivermead postconcussion symptom questionnaire. The secondary objective is to explore the neuropathophysiological changes that occur following rTMS in participants with PPCS using fNIRS. Exploratory objectives include determining whether rTMS treatment in participants with PPCS will also improve quality of life, anxiety, depressive symptoms, cognition, posttraumatic stress, and function secondary to headaches.

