#### Postprocessing fNIRS Data

Preprocessed data between 4 major brain regions (ie, left DLPFC, left motor cortex, right DLPFC, and right motor cortex) will be assessed using a coherence analysis at 0.04 to 0.1 Hz. Coherence will be calculated for all channels over the 4 regions. Coherence is defined as an estimate of a linear-time variant relationship between 2 signals at a particular frequency domain [19]. The coherence value used will be the maximum coherence between each combination of regions. The interregional coherence values will be quantified between the right and left DLPFC, the left and right motor cortex, the left DLPC and left motor cortex, and finally between the right DLPFC and right motor cortex [18].

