#### Statistical Analysis

The effect size of the RPQ score extrapolated from a similar study (*d*=0.77) [10] provided the basis for a power calculation performed with an alpha of .05, and 80% power suggested that 44 participants should be included in this study (22 per group). Anticipating a 20% attrition [10,22,55], 56 participants will be recruited for this study.

Descriptive statistics will be used to analyze baseline characteristics. A 2-way (treatment × time) mixed ANOVA will be used to assess whether any changes in clinical measurements and outcome parameters were the result of the interaction of type of treatment (real vs sham) and time. fNIRS data will also be analyzed using a 2-way mixed ANOVA where interregional coherence will act as the dependent variable, sham vs real TMS treatment will act as the between-subject variable, and brain region and assessment (ie, pre-TMS, post-TMS, 1-month follow-up, and 3-month follow-up) will act as the within subject variables. A *P* value of ≤.05 will be considered significant. A post hoc analysis will be used for exploratory measures. Simple effects testing using a Bonferroni correction will be performed when a significant group by time interaction is detected.

fNIRS data will be assessed to determine the location and magnitude of task-evoked changes in oxyhemoglobin, deoxyhemoglobin, and total hemoglobin at the left DLPC for each participant. Coherence of hemodynamic frequencies between major brain regions will also be quantified to observe brain connectivity during tasks as previous works have done [18,19]. Our group has previously attempted to decrease bias by restricting change in medication and other treatments throughout the trial [11]; however, it is unknown how some medications may influence rTMS and fNIRS data. Full patient characteristics, injury characteristics, and medication profile will be collected to better understand this bias.

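### The fNIRS coherence ANOVA, run in its usual complete-case form, would exclude a participant if one brain region loses all its channels at one visit; a mixed model would keep the remaining data

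*Protocol article*

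**What the plan says.** Three parts of the protocol article's Analysis section bear on this point.

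- **Preprocessing fNIRS Data** sets the discard rules: "channels that display low signal (below 90 dB) or have an oversaturated signal (above 140 dB) will be discarded", and then "Channels that have a signal to noise ratio less than 1 will also be discarded". No minimum number of surviving channels per region is given.
- **Postprocessing fNIRS Data** names four regions ("left DLPFC, left motor cortex, right DLPFC, and right motor cortex") and the score: "The coherence value used will be the maximum coherence between each combination of regions". Four pairs are analysed: the two DLPFCs, the two motor cortices, and the DLPFC with the motor cortex on each side. Each region therefore belongs to exactly two pairs.
- **Statistical Analysis** names the model: "fNIRS data will also be analyzed using a 2-way mixed ANOVA where interregional coherence will act as the dependent variable". Treatment is the between-subject factor, and "brain region and assessment (ie, pre-TMS, post-TMS, 1-month follow-up, and 3-month follow-up) will act as the within subject variables".

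The Abstract gives the status of this work: "The secondary objective is to explore the neuropathophysiological changes that occur following rTMS in participants with PPCS using fNIRS". Statistical Analysis also describes a second fNIRS readout, task-evoked hemoglobin changes at the left DLPFC, which does not use region pairs.

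**The concern.** Each rule is reasonable alone, but they fit together badly. The discard rules can in principle empty a region at a visit. A maximum over no channels has no value, so both pairs that use the region are unscored at that visit. The chosen model has a fully crossed within-subject layout, and its classical form needs every cell filled.

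A fault confined to 2 of 16 cells could therefore cost the whole participant. A missed fNIRS visit would have the same effect. The trial is small: 44 participants are planned for analysis after 20% attrition, and exclusions for signal loss would come on top of that. The coherence result would rest on the subset in whom every region was scorable at every visit.

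**Working it through.** **Inputs from the article.** 4 regions; 4 region pairs; 4 assessments; 44 participants (22 per group); 20% attrition; 56 recruited.

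**The plan's own figures.** Attrition reproduces by arm: 22 / 0.8 = 27.5, rounded up to 28, and 2 × 28 = 56. The 44 comes from an RPQ effect size (d = 0.77, alpha .05, 80% power); a one-sided two-sample t-test with 22 per arm has 80.7% power. It is not an fNIRS calculation. I use 44 only as the number of participants left after attrition. The article has no figure for fNIRS signal loss to reproduce.

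**Cells.** Coherence belongs to a pair of regions, so I read the region factor as the four pairs. Cells per participant = 4 pairs × 4 assessments = 16. Rest, finger tapping and working memory are recorded separately, so this is 16 per task condition. One empty region at one visit leaves 2 cells undefined and 16 − 2 = 14 valid.

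**Behaviour of the method.** I checked a simulated 4 × 4 within-subject layout with 10 participants (160 values, no treatment factor), removing two pairs at one visit for one participant. A standard repeated-measures ANOVA routine rejected the data as unbalanced and ran only after that participant was removed. A linear mixed model kept all 10 participants and 158 of 160 values.

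**Size, under assumption.** Let q be the chance that a region has no usable channel at a visit. The article does not give q; I assume 1%, 2% and 5%. A participant is complete only if all 4 × 4 = 16 region-visits are usable.

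- Independent failures: complete fraction f = (1 − q)^16.
- Clustered failures: f is the chance that none of 16 normal latent variables with pairwise correlation 0.5 falls below the q-quantile, by numerical integration. A simulation of 200,000 draws gave 0.910, 0.842 and 0.693, in close agreement.
- Persistent failures (a failed region stays failed at all visits): f = (1 − q)^4.

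| q | Independent: f; 44 × f | Clustered: f; 44 × f | Persistent: f; 44 × f |
|---|---|---|---|
| 1% | 0.851; 37.5 | 0.909; 40.0 | 0.961; 42.3 |
| 2% | 0.724; 31.8 | 0.842; 37.0 | 0.922; 40.6 |
| 5% | 0.440; 19.4 | 0.691; 30.4 | 0.815; 35.8 |

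The share of pair-visit cells that remain valid is (1 − q)^2 = 98%, 96% and 90% at the three values of q.

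**Standard error.** Relative to 44 complete participants, the factor for the arm contrast is √(1/f): 1.08, 1.18 and 1.51 if independent; 1.05, 1.09 and 1.20 if clustered; 1.02, 1.04 and 1.11 if persistent. A mixed model would also lack the undefined cells, so the avoidable part is smaller than these factors.

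**How low q could be.** One surviving channel per region is enough for a score. With an assumed 4 channels per region failing independently, a 20% channel failure rate gives q = 0.2^4 = 0.16% and f = 0.9984^16 = 97%. A 30% rate gives q = 0.3^4 = 0.81% and f = 0.9919^16 = 88%. Correlated failure within a region would raise q.

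**The case against.** The strongest objection is that this is an omission. Minimum channel counts, scoring of an unusable region and handling of incomplete imaging data are details that a condensed article commonly leaves to the full protocol or SAP, neither of which is shown. That stands for the missing-data rule itself, and its absence is not the point. The article does, however, name the model and its within-subject factors. An SAP that followed that text literally would inherit the problem.

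A reader might infer that the plan drops incomplete participants. It does not say so. Exclusion is what a mixed ANOVA does in its usual complete-case form; imputation or a mixed-model fit would avoid it.

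A reader might also infer that a large loss is to be expected. The documents do not support that. They give no discard rate, the text gives no number of channels per region, and the optode figure is not shown. The lowest counts also require independent failure over 16 region-visits in the same head, which is the pessimistic pattern of the three.

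Finally, it would be wrong to treat coherence as the whole secondary objective, or to say that only participants with clean signal would remain. The objective covers fNIRS generally and is worded as exploratory, task-evoked hemoglobin is a second readout, and a region needs only one usable channel. These objections limit the size and reach of the point; they do not remove the mismatch between the discard rule and the model.

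**Conclusion.** The point holds conditionally. If the coherence ANOVA is run on complete cases, one empty region at one visit, or one missed fNIRS visit, excludes the participant. In the first case 14 valid values are lost because 2 are undefined.

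The loss cannot be sized from the documents. Over an assumed failure rate of 1% to 5% per region-visit, expected complete cases out of 44 run from 42.3 (1%, persistent failure) down to 19.4 (5%, independent failure). With several channels per region the loss may be negligible. These figures rest on the assumed rate, the assumed failure pattern, 44 participants otherwise complete, and complete-case analysis.

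The effect is confined to the coherence analysis within an exploratory secondary objective. The task-evoked hemoglobin readout and the primary RPQ analysis are not touched by this signal-loss problem. The change is still worth making, because the alternative costs little and keeps valid data.

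**What to change.** In Statistical Analysis, replace the mixed ANOVA for coherence with a linear mixed model fitted by restricted maximum likelihood, separately for each task condition. Use treatment, assessment, region pair and their interactions as fixed effects, and participant and participant-by-visit as random effects. Use all available pair-visits. Treat a pair as missing only at a visit where one of its regions has no surviving channel. Report the number of unscorable pair-visits by arm.

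The cost is a few sentences of plan text and slightly different model code, with no new data, visits or participants. The downside is reliance on a missing-at-random assumption; the counts by arm would at least show whether signal loss differs between groups.

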#### Postprocessing fNIRS Data

Preprocessed data between 4 major brain regions (ie, left DLPFC, left motor cortex, right DLPFC, and right motor cortex) will be assessed using a coherence analysis at 0.04 to 0.1 Hz. Coherence will be calculated for all channels over the 4 regions. Coherence is defined as an estimate of a linear-time variant relationship between 2 signals at a particular frequency domain [19]. The coherence value used will be the maximum coherence between each combination of regions. The interregional coherence values will be quantified between the right and left DLPFC, the left and right motor cortex, the left DLPC and left motor cortex, and finally between the right DLPFC and right motor cortex [18].

#### Statistical Analysis

The effect size of the RPQ score extrapolated from a similar study (*d*=0.77) [10] provided the basis for a power calculation performed with an alpha of .05, and 80% power suggested that 44 participants should be included in this study (22 per group). Anticipating a 20% attrition [10,22,55], 56 participants will be recruited for this study.

Descriptive statistics will be used to analyze baseline characteristics. A 2-way (treatment × time) mixed ANOVA will be used to assess whether any changes in clinical measurements and outcome parameters were the result of the interaction of type of treatment (real vs sham) and time. fNIRS data will also be analyzed using a 2-way mixed ANOVA where interregional coherence will act as the dependent variable, sham vs real TMS treatment will act as the between-subject variable, and brain region and assessment (ie, pre-TMS, post-TMS, 1-month follow-up, and 3-month follow-up) will act as the within subject variables. A *P* value of ≤.05 will be considered significant. A post hoc analysis will be used for exploratory measures. Simple effects testing using a Bonferroni correction will be performed when a significant group by time interaction is detected.

fNIRS data will be assessed to determine the location and magnitude of task-evoked changes in oxyhemoglobin, deoxyhemoglobin, and total hemoglobin at the left DLPC for each participant. Coherence of hemodynamic frequencies between major brain regions will also be quantified to observe brain connectivity during tasks as previous works have done [18,19]. Our group has previously attempted to decrease bias by restricting change in medication and other treatments throughout the trial [11]; however, it is unknown how some medications may influence rTMS and fNIRS data. Full patient characteristics, injury characteristics, and medication profile will be collected to better understand this bias.

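### The fNIRS coherence model is called 2-way but lists three factors, and its outcome, a maximum over surviving channels, depends on how many channels survive

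*Protocol article*

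**What the plan says.** The model is set out in one sentence of the Statistical Analysis section. It begins "fNIRS data will also be analyzed using a 2-way mixed ANOVA where interregional coherence will act as the dependent variable", continues "sham vs real TMS treatment will act as the between-subject variable", and ends with "brain region and assessment (ie, pre-TMS, post-TMS, 1-month follow-up, and 3-month follow-up) will act as the within subject variables".

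The outcome is fixed under Postprocessing fNIRS Data. Coherence is calculated for all channels over four regions in the band 0.04 to 0.1 Hz, and "The coherence value used will be the maximum coherence between each combination of regions". Four region pairs are named. Before that, under Preprocessing fNIRS Data, channels below 90 dB or above 140 dB are dropped, and "Channels that have a signal to noise ratio less than 1 will also be discarded".

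On the recordings, the Functional Near-Infrared Spectroscopy section says "Data will be collected for 5 minutes at rest and then during a finger tapping exercise and working memory tasks". Tapping itself is at 1 Hz. Its block design is: "The participant will alternate between tapping for 10 seconds and resting for 15 seconds, which will be repeated 10 times". The Statistical Analysis section adds: "Coherence of hemodynamic frequencies between major brain regions will also be quantified to observe brain connectivity during tasks".

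**The concern.** The label and the factor list cannot both be right. Taken literally, a 2-way model would have to average over the region pairs or be fitted to each pair separately. The factor list instead implies one model with region inside it. These give different tests of the secondary objective. The follow-up rule (Bonferroni-corrected simple effects after a significant group by time interaction) is also written as if only one interaction with treatment and time existed. A three-factor model has two such terms, with and without region.

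The second matter is the outcome itself. The number of channel pairs behind each maximum is whatever survives quality control. Two recordings with the same underlying connectivity but different signal quality therefore have different expected outcomes. With 22 participants per group planned, avoidable noise matters, and any channel loss that differs between arms over time would look like a treatment effect.

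The third matter is smaller. In the tapping condition a block-locked response shared by two regions can raise their coherence without any coupling between them.

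**Working it through.** **1. Model order.** The plan's figure is 2. The factors listed in the same sentence are treatment (2 levels, between subjects), brain region (4 region pairs, within) and assessment (4 levels, within). That is 1 + 2 = 3, so the plan's figure is not reproduced. A full model with k factors has 2^k − 1 effects:
- two-way: 2² − 1 = 3
- three-way: 2³ − 1 = 7

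Of the seven, two ask whether change over time differs by arm: treatment × assessment, and treatment × assessment × region pair.

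**2. Maximum against mean.** The article text gives no usable channel count, segment length or noise model, so these inputs are assumptions. Two regions were simulated as unrelated AR(1) signals (coefficient 0.95), 250 s at 5 Hz. Welch coherence with 50% overlap was averaged over 0.04–0.1 Hz, with 150 runs per setting.

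| Channels per region | Pairs | Mean maximum, 50 s segments | Mean maximum, 100 s segments |
|---|---|---|---|
| 2 | 4 | 0.18 | 0.35 |
| 4 | 16 | 0.24 | 0.42 |
| 6 | 36 | 0.27 | 0.46 |

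The average over pairs did not move with channel count: 0.12 with 50 s segments and 0.26 with 100 s segments. Going from 16 pairs to 4 lowers the expected maximum by 0.24 − 0.18 = 0.06 (50 s) or 0.42 − 0.35 = 0.07 (100 s), with no change in true coupling. The sizes depend on the assumptions. The direction does not: adding candidates cannot lower a maximum.

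**3. Task frequencies against the band of 0.04–0.1 Hz.**
- Tapping movement: 1 Hz, ten times the upper edge, so outside the band.
- Tapping block: 10 + 15 = 25 s; 1/25 = 0.04 Hz, on the lower edge; second harmonic 2/25 = 0.08 Hz, inside.
- 2-back block: 20 × 2 + 20 = 60 s; 1/60 = 0.0167 Hz, below the band. Only higher harmonics, such as 4/60 = 0.067 Hz, fall inside, so the point chiefly concerns tapping.

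Under an assumed double-gamma haemodynamic response, 99.6% of the tapping-evoked power lies in the band with its edges included: 96.7% at 0.04 Hz and 2.9% at 0.08 Hz. Whether the edge counts therefore matters.

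Adding this response to the unrelated channels changed average coherence as follows:
- evoked SD half the noise SD (0.25/1.25 = 20% of variance): 0.12 to about 0.17 with 50 s segments; 0.26 to 0.31 with 100 s
- evoked SD equal to the noise SD (1/2 = 50% of variance): 0.12 to 0.32; 0.26 to 0.40

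**The case against.** The strongest reply is that the factor list is clear and only the label is wrong, so an analyst would fit the three-factor model anyway. That is the likeliest intention. It limits the harm but leaves a wrong model order in the text, with no statement of which interaction is the test.

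On the outcome, both arms pass through the same rejection rules in a blinded, randomised trial, so varying channel counts should mostly add noise. That stands. Nothing in the article shows that channel loss would differ by arm over time, and bias is conditional on that.

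On tapping, both arms do the same task, so block-locked coherence does not by itself produce a false treatment × assessment effect. That stands too. What remains is interpretation. The Introduction expects an improved haemodynamic response in participants who improve, and if stimulation changes evoked amplitude, tapping coherence would move with it. The separate analysis of evoked haemoglobin changes helps, but does not take the evoked part out of the coherence.

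A reader might infer twelve uncorrected tests (4 pairs × 3 conditions) and a familywise error of 1 − 0.95^12 = 46%. The text does not support this, because region is a factor inside the model. If one model were fitted per condition, a given term would be tested three times: 1 − 0.95³ = 14.3% if independent, and the same participants supply all three conditions, so independence is doubtful. A reader might also say that the three conditions are ignored. How condition enters is detail that an article may leave to the fuller plan, and separate models per condition fit the text.

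**Conclusion.** The point holds in a limited form. That the model order is misstated follows from one sentence and needs no assumption. That the outcome depends on the number of surviving channels follows from taking a maximum after quality rejection. It assumes only that the maximum runs over channel pairs and that rejection is applied recording by recording, which is the natural reading. The shift of about 0.06 to 0.07 between 16 and 4 pairs is illustrative and should not be quoted as the trial's own error.

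The tapping-block point is a caution on one condition. A reader might conclude that the coherence tests cannot isolate connectivity at all. The article does not support that: resting recordings have no task cue, and the movement frequency of 1 Hz is far outside the band.

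The effect is confined to the secondary objective, which the article describes as exploring. The primary RPQ analysis is untouched.

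**What to change.** 1. Replace the 2-way label with a three-way mixed model, treatment × assessment × region pair. Name treatment × assessment as the key term, and say how the three-way interaction will be read.
2. Replace the maximum with the mean Fisher-z coherence over channel pairs, using a consistent channel set across each participant's visits where possible. Keep the maximum as a sensitivity analysis. Report retained pairs by arm and visit, so that readers can see whether loss was balanced.
3. Interpret tapping coherence as a mixture of evoked response and coupling, or add a sensitivity analysis with the evoked response removed first.

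The cost is wording and scripting; no new data are needed. There are two real downsides. Results become less directly comparable with earlier work by the group that used the maximum, which the sensitivity analysis partly offsets. And a consistent channel set lets one poor recording remove good channels from the same participant's other visits, which is why it should apply where possible and not absolutely.
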